# Enhancing uptake of the Canadian Prison Needle Exchange Program using a non-randomized stepped-wedge cluster type 1 hybrid implementation trial: The NEXUS study protocol

**DOI:** 10.1016/j.conctc.2026.101642

**Published:** 2026-04-28

**Keywords:** Prisons, Needle exchange programs, Implementation science, HIV, Hepatitis C, People who inject drugs

## Abstract

**Background:**

Prison needle exchange programs (PNEPs) are evidence-based harm reduction interventions that decrease bloodborne virus transmission by reducing the sharing of injection equipment. Canada introduced PNEPs in nine of its 43 federal prisons in 2018-2019; however, uptake is low. This implementation gap undermines program effectiveness, jeopardising individual- and population-level benefits of the program. This stepped-wedge cluster non-randomised type 1 hybrid implementation trial will evaluate whether the Network for the Improvement of Addiction Treatment (NIATx) bundle of implementation strategies and tools increases PNEP uptake.

**Methods:**

All nine prisons were allocated non-randomly to three sequences; each sequence is activated at six-month intervals. Over 24 months, each prison will use NIATx tools to address site-specific barriers to PNEP determined during preliminary work. Stepped implementation will be evaluated using the Reach, Effectiveness, Adoption, Implementation, Maintenance (RE-AIM) framework of the Practical Robust Implementation and Sustainability Model (PRISM). The primary effectiveness outcome is PNEP uptake (i.e., number of participants enrolled on the program). Secondary effectiveness outcomes include number of kits distributed (evidencing active participation) and individuals tested and diagnosed with bloodborne virus infections, including HIV and hepatitis B and C virus (to assess harm reduction impact). Staff surveys and focus groups during and post-implementation, respectively, will explore individual- and organisational-level factors influencing implementation and maintenance.

**Discussion:**

We anticipate that NIATx tools will improve uptake of PNEPs among people who inject drugs in Canadian federal prisons. Findings are expected to inform scale-up across remaining Canadian prisons, support long-term sustainability, and inform global advocacy for prison needle and syringe programs.

## Introduction

1

People who inject drugs are at elevated risk of bloodborne virus infections (e.g., HIV, hepatitis C virus [HCV]), primarily through sharing of injection equipment [1]. This population is also disproportionately incarcerated, with lifetime injection drug use prevalence 50 times higher among people in prison and other closed settings than in the general population [2]. While injection frequency typically decreases during incarceration [3], limited access to sterile injection equipment means that the risk of bloodborne virus acquisition per injecting episode is higher in prisons than in the community [4]. Among people who inject drugs, recent incarceration is associated with a higher risk of HIV and HCV acquisition [5], underscoring prisons as key settings for the prevention of bloodborne virus transmission [[6], [7], [8], [9]].

The World Health Organization and the United Nations Office on Drugs and Crime recommend prison needle exchange programs (PNEPs) as essential components of HIV/HCV prevention strategies [6], based on unequivocal findings that they reduce transmission in community settings by reducing reuse of injecting equipment [10,11]. As of 2025, PNEPs were available in only 11 countries globally, often as pilot programs [12], reflecting sub-optimal implementation, reach, and scale-up. Structural barriers including stigma, political opposition, security concerns, failure to protect participant confidentiality, and restrictive policies have limited broader adoption [13]. This has undermined efforts to reduce the HIV and HCV burden among people who inject drugs and to meet HIV and HCV reduction targets set by UNAIDS and the World Health Organization [14,15].

Research on effective implementation is needed to increase PNEP engagement among people who inject drugs in prison and support sustainable, scalable programs. With only Ukraine having introduced PNEPs in the past decade [13], evidence of program effectiveness is needed to inform broader adoption globally [16]. Canada provides a unique setting for this work, as it is one of few countries where PNEPs are implemented. The Canadian PNEP is cost-effective [17], but it is estimated that fewer than 10% of people who inject drugs in prison access it [18]. This implementation gap is driven by multiple, intersecting barriers, involving the individual, staff, the prison environment itself, and enacted policies governing PNEP. Stigma remains a major issue at all implementation levels and is exacerbated by limited program confidentiality, with participation visible to both healthcare and correctional staff [19]. Staff opposition to the program is often shaped in part by safety concerns, including a fear of needlestick injuries, despite no reported incidents since program inception [13]. Public opposition, including from members of the Union of Canadian Correctional Officers, further limits program uptake, while broader zero-tolerance approaches to drug use in prison contradict patient-centred harm reduction principles [[19], [20], [21], [22]].

The **N**eedle **EX**change **U**ptake **S**tudy (NEXUS) is a type 1 hybrid effectiveness-implementation trial that aims to evaluate the PNEP in Canadian federal prisons via a stepped wedge design, while simultaneously examining contextual determinants. We will apply the Network for the Improvement of Addiction Treatment (NIATx) model as a blended implementation strategy to enhance PNEP delivery.

## Methods

2

### Context

2.1

Canadian federal prisons are overseen by Correctional Service Canada and house people serving sentences of two years or longer. Prior to the introduction of PNEPs in Canada, research indicated that drugs were readily available in federal prisons and that sharing of needles and other injection equipment was common [23]. Data collected since program implementation suggest that approximately 60% of people who inject drugs in prison share injecting equipment [24]. It is estimated that 0.7% of people incarcerated in Canadian federal prisons are living with HIV, and 22% have evidence of prior or current HCV infection [25].

In response to legal action, Correctional Service Canada introduced PNEPs in nine of its 43 federal prisons in 2018-2019. In line with the 2024-2030 Government of Canada's Sexually Transmitted and Blood-Borne Infection Action Plan [26], PNEPs were expanded to five additional prisons between 2024 and 2025 ([name], personal communication, 18 September 2025). The program is intended to reduce sharing of injection equipment, transmission of bloodborne viruses, and injecting-related skin infections [27]. The PNEP sits within Correctional Service Canada's broader harm reduction program that includes opioid agonist therapies, HIV and HCV treatment, and HIV pre-exposure prophylaxis [27]. Participation in the PNEP is contingent on a ‘Threat Risk Assessment’, a mandatory security approval process unique to Canada's healthcare delivery model [20]. To date, uptake of the PNEP by people who inject drugs in Canadian federal prisons is estimated as less than 10% of those who might benefit from it [18], reflecting an implementation gap that limits program effectiveness.

### Implementation framework

2.2

We used the Practical, Robust Implementation and Sustainability Model (PRISM) [28] to frame our pre-implementation assessment of PNEP within Correctional Service Canada (Fig. 1). PRISM is a process/determinant framework that maps how multilevel context shapes implementation across four domains: 1) organizational and patient characteristics; 2) organizational and patient perspectives of the intervention; 3) external environment (including policy instruments such as the Threat Risk Assessment); and 4) implementation and sustainability infrastructure [33]. PRISM integrates the Reach, Effectiveness, Adoption, Implementation, and Maintenance (RE-AIM) framework [34,35], which provides the structure for evaluating implementation, including participation and clinical/harm reduction measures (Effectiveness), site and staff uptake (Adoption), fidelity (Implementation), and sustainability (Maintenance).

**Fig. 1 fig1:**
[figure not shown]
Study implementation logic model. **Notes.** Adapted from https://re-aim.org/learn/prism/. ∗Organisational characteristics will be assessed in staff surveys; organisational perspectives about the PNEP were explored in † Lafferty et al. [29], ‡ Kronfli et al. [30], and § Kronfli et al. [31]; individual perspectives explored in § Kronfli et al. [31] and ‖ Lafferty et al. [32]; and external environment explored in ¶ Kronfli et al. [20].

Guided by PRISM, our pre-implementation work using nominal group technique identified site-specific barriers among multi-level stakeholders [30,32]. Correctional officers and healthcare workers identified key barriers for people who inject drugs, including bullying and coercion from peers, fear of being targeted or reprimanded due to drug use from correctional officers, the program's lack of confidentiality/privacy, and the long and complex corrections-mandated Threat Risk Assessment [30]. People who inject drugs in prison similarly reported fear of being targeted by correctional officers or repercussions from correctional officers due to drug use, lack of confidentiality/privacy, and the application process with its strict eligibility criteria as key barriers to participation [32]. Among institutional heads, implementation was framed by structural tensions between harm reduction goals and ‘zero tolerance’ custodial mandates [20,29]. The Threat Risk Assessment was characterized as prioritizing institutional security over public health, and stakeholders proposed transferring PNEP authority entirely to healthcare services and streamlining the approval process [20,31]. Together, these findings informed an *a priori* logic for how contextual features were expected to shape implementation outcomes and will continue to inform process-improvement activities tailored to each prison's context during the trial.

### Overall design

2.3

This protocol follows the StaRI Statement for implementation studies and incorporates relevant items of the CONSORT Statement extension for stepped wedged cluster randomised trials (Appendices A and B) [36,37]. NEXUS is a type 1 hybrid effectiveness-implementation trial designed to increase uptake of the Canadian PNEP among people who inject drugs in prison by addressing barriers to participation. Type 1 hybrid studies focus primarily on measuring the effectiveness of the intervention, and secondarily explore implementation-related factors [38]. They are suitable when there is existing evidence that the intervention is effective in other settings or populations, supporting its applicability to a new context [39].

All nine federal prisons with an established PNEP at the time of the trial were enrolled, comprising five women's prisons (five multi-level security) and four men's prisons (one minimum security, one medium security, one maximum security, and one multi-level security) (Table 1). Using a stepped-wedge cluster design, each prison will transition from standard of care to NIATx activities over the study period. This design incorporates a six-month baseline period of pre-NIATx data collection which serves as the control condition. We chose a cluster design because NIATx targets organisational-level process improvements that cannot be delivered at the individual level. In a stepped-wedge trial, the effect estimate comparing NIATx to standard of care combines both within-cluster (i.e., outcomes before vs. after implementation within the same prison) and between-cluster (i.e., prisons with the intervention vs. without the intervention at a given time) effects [40]. A key challenge in this design is that outcomes may change over time due to factors unrelated to the intervention [41]. Ideally, the order in which each cluster receives the intervention is randomised to mitigate this potential source of bias.

**Table 1 tbl1:** Baseline prison needle exchange program participation and prison population size, September 2024-February 2025.

Group	Prison	Province	Security level	Gender	Sep. 2024	Oct. 2024	Nov. 2024	Dec. 2024	Jan. 2025	Feb. 2025
1	Atlantic Institution	New Brunswick	Maximum	Men	17/247 (6.9%)	14/236 (5.9%)	17/224 (7.6%)	17/225 (7.6%)	18/237 (7.6%)	17/225 (7.6%)
	Dorchester Penitentiary	New Brunswick	Multi	Men	10/350 (2.9%)	10/359 (2.8%)	12/362 (3.3%)	14/369 (3.8%)	13/365 (3.6%)	13/368 (3.5%)
	Nova Institution for Women	Nova Scotia	Multi	Women	∼/88 (≤5.7%)	11/86 (12.8%)	9/86 (10.5%)	11/89 (12.4%)	12/93 (12.9%)	17/89 (19.1%)
2	Edmonton Institution for Women	Alberta	Multi	Women	∼/166 (≤3.0%)	∼/169 (≤3.0%)	∼/175 (≤2.9%)	∼/176 (≤2.8%)	∼/177 (≤2.8%)	∼/187 (≤2.7%)
	Grand Valley Institution for Women	Ontario	Multi	Women	∼/220 (≤2.3%)	∼/221 (≤2.3%)	∼/213 (≤2.3%)	∼/228 (≤2.2%)	∼/228 (≤2.2%)	∼/226 (≤2.2%)
	Mission Institution	British Columbia	Medium	Men	14/297 (4.7%)	13/295 (4.4%)	13/289 (4.5%)	13/296 (4.4%)	17/292 (5.8%)	15/294 (5.1%)
3	Fraser Valley Institution for Women	British Columbia	Multi	Women	∼/102 (≤4.9%)	∼/98 (≤5.1%)	∼/104 (≤4.8%)	∼/108 (≤4.6%)	∼/102 (≤4.9%)	∼/104 (≤4.8%)
	Établissement Joliette	Quebec	Multi	Women	∼/103 (≤4.9%)	∼/108 (≤4.6%)	∼/108 (≤4.6%)	∼/106 (≤4.7%)	∼/113 (≤4.4%)	∼/113 (≤4.4%)
	Joyceville Institution	Ontario	Minimum	Men	∼/241 (≤2.1%)	∼/250 (≤2.0%)	∼/260 (≤1.9%)	∼/267 (≤1.9%)	∼/282 (≤1.8%)	∼/278 (≤1.8%)

**Notes.** % of total prison population. ∼ suppressed as count 0≤n ≤ 5; % for these time points are presented as ≤5/total population.

### Allocation and sequence generation

2.4

Although the nine prisons were initially randomised into three sequences, logistical issues required minor adjustments, with one prison per sequence exchanged to accommodate travel and scheduling restrictions. Potential bias from the lack of randomisation will be considered in the interpretation of results. The three sequences are activated at six-month intervals. Each sequence undergoes pre-implementation activities, consisting of NIATx training conducted in the final three months of the six-month baseline control period, followed by 24 months of NIATx implementation, and 12 months of maintenance (Fig. 2). The study commenced in September 2024, with sequence 1 beginning pre-implementation activities in December 2024.

**Fig. 2 fig2:**
[figure not shown]
Study timeline.

### Implementation strategies and tools

2.5

Variation in barriers across key stakeholders (i.e., people in prison, staff) and the nine prisons identified in our pre-implementation work led us to select the NIATX model, a blended implementation strategy. NIATx combines practice facilitation, collaborative learning, coaching, rapid cycle change testing (i.e., iterative testing of small changes in practice to refine implementation), and data-driven audit and feedback [42,43], and aligns with the Expert Recommendations for Implementing Change (ERIC) taxonomy [44]. NIATx has been used successfully to improve service delivery and scale up evidence-based interventions, including opioid agonist therapies [[45], [46], [47]]. To our knowledge, NIATx has not previously been applied to harm reduction services in prisons. By extending NIATx into this domain, we adapt a proven blended implementation strategy for organisational change to a carceral context, emphasizing workflow redesign, data-driven decision-making, and multi-level engagement between correctional, clinical, and public health stakeholders, to optimise adoption, implementation, and maintenance.

We will use NIATx to enhance PNEP delivery by addressing site-specific barriers identified in our pre-implementation work. Each prison will establish a three-person change team, including a designated leader and representatives from both healthcare (e.g., nurse) and corrections (e.g., correctional manager). Throughout the study, quarterly meetings with Correctional Service Canada will help ensure ongoing executive sponsorship and be used to monitor the PRISM external environment, including leadership changes, policy shifts, and variations in federal funding, which could influence implementation.

#### Pre-implementation phase

2.5.1

During this phase, change teams from each sequence of three prisons will participate in a one-day, in-person training session with the study team (including a NIATx coach) on the principles of NIATx. The session will introduce the NIATx bundle of implementation strategies and tools (e.g., rapid cycle testing, walk-throughs, flowcharting) and support teams in identifying potential plan-do-study-act change projects based on site-specific rank-ordered barriers determined with multi-level stakeholders *a priori* [[30], [31], [32]]. Group activities will help solidify these concepts. For example, change teams will practice conducting ‘walk-throughs’ to understand the perspective of potential PNEP participants and use ‘flowcharting’ to map how PNEP activities are currently delivered in their respective prisons. These activities are intended to help change teams reframe barriers as opportunities for process improvement. Teams will be encouraged to use NIATx tools throughout the implementation phase to iteratively identify new or previously unrecognised barriers and generate new ideas for change projects.

#### Implementation phase

2.5.2

A NIATx coach will lead activities during the 24-month implementation phase. The coach, members of the research team, and each prison change team will meet monthly via videoconference to use NIATx tools to guide process improvement. Each month, the change team will plan and implement a change project using a plan-do-study-act framework, tailored to address site-specific barriers identified through nominal group technique, walk-throughs, and/or flowcharting. For example, some may focus on increasing awareness of the PNEP through discussions with new prison admissions, while others may address the lengthy PNEP application process [30,32]. The role of the NIATx coach in this process is to guide rather than direct, building the capacity of each team to sustain process improvements beyond the implementation phase [43]. Key coaching elements include providing encouragement, positive reinforcement, and troubleshooting to reduce frustration and sustain momentum during the change project process [43]. We anticipate some staff turnover during the implementation phase; when this occurs, departing team members will be replaced by staff from the same department (i.e., health or corrections), who will be trained in the NIATx tools.

Developed in collaboration with Correctional Service Canada, a PNEP ‘data dashboard’ will allow change teams to make data-driven decisions following implementation of their monthly change projects. The dashboard is updated monthly and provided to change team members prior to each coaching call. For example, the number of PNEP applications will be tracked over time to evaluate PNEP uptake, while median time to participation approval will be used to understand timeliness of program access. Change teams will review these data monthly to determine whether to adopt, adapt, or abandon the changes implemented through rapid cycling testing. Over the course of the implementation phase, there will be approximately 24 monthly change projects. A NIATx fidelity form is completed after each coaching call.

Change teams at activated sites will also meet face-to-face every six months for collaborative learning, which aims to facilitate peer-to-peer learning through the sharing of progress, challenges, and promising practices. These collaborative meetings will also support knowledge transfer from the more experienced change teams to the newer teams, aligning with PRISM's Implementation and Sustainability Infrastructure which considers sharing of promising practices a key element.

#### Maintenance phase

2.5.3

During the 12-month maintenance phase, the NIATx coach will transition facilitation duties to the change leader at each site. The goal is that the internal NIATx coach will oversee continued use of NIATx tools to improve (or sustain) PNEP uptake while continuing to interact with all stakeholder groups.

### Participants

2.6

All people in the nine prisons who self-report a history of injection drug use are eligible to request participation in the PNEP. Due to ethical and privacy concerns, only aggregate (cluster-period-level) data without individual-level identifiers are available for analysis. Consequently, while this design constitutes an ‘open cohort’ [48], we are unable to track specific individuals over time, so data will be analyzed cross-sectionally despite repeated assessment of some of the same individuals. We anticipate that there will be participant overlap between months, meaning the population composition will remain relatively stable over time.

### Study outcomes

2.7

The RE-AIM framework will guide evaluation of PNEP effectiveness and implementation outcomes [34] (Table 2).

**Table 2 tbl2:** Data measures mapped to the RE-AIM framework.

Domain	Definition	Measure	Data source	When measured	Frequency of measurement	Analysis type
Effectiveness	Primary: PNEP uptake	Primary: Count of PNEP participation	Correctional Services Canada	PI, IP, MP	Monthly	Quantitative
	Secondary: a PNEP coverage b Uptake of bloodborne virus services c Uptake of opioid agonist therapies	Secondary: a Count of PNEP kits distributed b Count of people screened, diagnosed, and treated for HIV/HBV/HCV c Count of enrolees on opioid agonist therapies				
Adoption	Increase in the number and/or availability of PNEPs in other Canadian federal prisons	a Number of prisons newly initiating PNEP services b Increased hours of operation of PNEP services	Correctional Services Canada	IP, MP	N/A	Quantitative
Implementation	PNEPs delivered as intended and with fidelity	a Fidelity to NIATx b Individual and organizational factors affecting implementation	b NIATx fidelity checklist and problem indicators subscale c Staff surveys	a IP b IP, MP	Every six months	Quantitative
Maintenance	Extent to which PNEPs are sustained after implementation phase	Maintenance of changes; barriers to maintenance; resource allocation	Nominal group technique	MP	Start and end of MP (∼6-9 months apart)	Mixed

**Abbreviations:** CSC = Correctional Service Canada; PI = pre-implementation phase; IP = implementation phase; MP = maintenance phase.

#### Effectiveness outcomes

2.7.1

The primary effectiveness outcome in this type 1 hybrid trial is PNEP uptake, defined as a monthly count of PNEP participants divided by the total prison population. Participation is a practical, measurable proxy indicator for PNEP effectiveness, capturing engagement with the program. We acknowledge, however, that high PNEP participation alone does not guarantee that all intended benefits of the program are achieved, particularly in the context of barriers to participation (e.g., confidentiality, stigma). Secondary effectiveness outcomes were selected accordingly and include PNEP coverage (number of needle/syringe kits distributed), opioid agonist therapy uptake (number of people receiving medication), and the numbers of people tested, diagnosed, and treated for bloodborne viruses (HIV, HCV, and hepatitis B virus), each expressed as a monthly count per total prison population. Data will be extracted by Correctional Service Canada at monthly intervals.

#### Implementation outcomes

2.7.2

Adoption will be documented as (1) the number of new federal prisons that introduce PNEP after the initiation of our study, and (2) expansion of PNEP operating hours, both of which reflect increased PNEP access. These metrics will be monitored through conversations with Correctional Service Canada leadership.

Fidelity will be monitored after every coaching call during the implementation period using an adapted NIATx fidelity checklist. This includes eight items (possible score: 0-3) that relate to structure and process (Appendix C). Structural items capture the role of leadership in NIATx, while process items capture how the change team uses the plan-do-study-act rapid cycle testing activities to improve PNEP implementation. A fidelity score of ≥80% (i.e., ≥19/24) will be considered ‘high’. A five-item problem indicators subscale (Appendix D) will complement the checklist to quantify the magnitude of any issues.

Staff attitudes and organisational characteristics will be captured through surveys administered every six months during all phases of the trial to all healthcare and correctional staff at participating prisons. Surveys include sociodemographic information (e.g., gender, sex, education), staff knowledge and perceptions of PNEP, and several validated brief scales. Work satisfaction and stress will be measured using the ProQOL-5 [49]; COPAN-5 will assess interprofessional collaboration [50]; the Resistance to Change Scale will measure routine seeking, emotional reaction, short term focus and cognitive rigidity [51]; the Social Dominance Scale (SDO_7_) will measure preference for group based hierarchy and inequality [52]; the Attitudes Towards Rehabilitation and Punishment scale will assess the extent to which staff believe that individuals should be punished for their drug use [53]; the Brief Substance Abuse Attitude Survey will capture broader attitudes towards drug use [54]; the Implementation Climate Scale will be used to capture issues relating to PNEP implementation [55]; the Implementation Leadership Scale will assess perspectives on Correctional Service Canada leadership in implementing PNEP [56]; and the Readiness to Change scale will capture staff motivation and organisational climate [57]. Responses will be linked over time using a unique anonymized identifier.

Maintenance will be examined in focus groups using nominal group technique at the beginning and end of the maintenance phase. The same stakeholder groups from preliminary work will participate in each prison: incarcerated individuals (peer advocates and potential and current PNEP users), correctional officers, and healthcare workers. Each group will include 8-10 participants (the ideal size for nominal group technique [58]), with 36 groups in total (4 groups of stakeholders x 9 prisons). Nominal group technique ensures equitable participation in settings where a power imbalance may exist [59]. Focus group prompts will address barriers to sustaining PNEP process changes and strategies required to support ongoing improvements.

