#### Planned subgroup analyses

2.8.4

We will assess whether the effect of NIATx on PNEP uptake differed by prison gender by including interaction terms between gender and the intervention and period effects. This is relevant because while lifetime injection drug use is higher among women than men in Canadian federal prisons [63], baseline uptake of PNEP in women's prisons is lower. This analysis is exploratory and intended to generate a hypothesis regarding gender as a potential effect modifier.

We will also explore the effects of fidelity to NIATx (measured using the fidelity checklist) and staff characteristics (e.g., readiness to change, attitudes towards people who use drugs) on implementation by including these variables as time-varying predictors in the models. This approach will allow us to assess whether improvements in fidelity or changes in staff attitudes over time are associated with increased effectiveness (i.e., higher PNEP participation), as has been observed in previous studies [64,65].

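### The two forms of the cut-off for high NIATx fidelity disagree: 19/24 is 79.2%, so a score of exactly 19 is high under one form and not under the other

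*Protocol article*

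**What the plan says.** Section 2.7.2 of the protocol article describes the fidelity instrument: "This includes eight items (possible score: 0-3) that relate to structure and process", with the checklist itself placed in Appendix C. It then fixes the cut-off: "A fidelity score of ≥80% (i.e., ≥19/24) will be considered" high. The wording presents the raw score as a restatement of the percentage. No rounding rule is given, and nothing says which form takes precedence.

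On timing, the same section states: "Fidelity will be monitored after every coaching call during the implementation period using an adapted NIATx fidelity checklist". Section 2.5.2 (Implementation phase) makes those calls monthly: "The coach, members of the research team, and each prison change team will meet monthly via videoconference". Table 2 gives a six-monthly frequency for the Implementation row, which includes fidelity.

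On use, Section 2.8.4 (Planned subgroup analyses) states: "We will also explore the effects of fidelity to NIATx (measured using the fidelity checklist) and staff characteristics". Fidelity is to enter the models there as a time-varying predictor. The section does not say whether it enters as a score or as a high/not-high indicator.

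**The concern.** A pre-specified cut-off should classify each score in one way only. Here one sentence gives a percentage and a raw score as equivalents, and on the article's own figures they are not. Two analysts working from the same sentence could report different proportions of high-fidelity calls, each with textual support.

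Fidelity is a named measure in the Implementation domain of RE-AIM in Table 2, and this is the only numerical cut-off that Section 2.7.2 gives for it. If the choice between the two forms is left until the scores have been seen, a threshold meant to be fixed in advance becomes a post hoc one.

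**Working it through.** **Inputs**

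- Number of items: 8 (Section 2.7.2).
- Score per item: 0 to 3 (Section 2.7.2).
- Stated cut-off: ≥80%, given as equal to ≥19/24 (Section 2.7.2).
- Assumption: totals are whole numbers. Appendix C is not among the documents at hand, so this is not confirmed.

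**Step 1. Reproduce the denominator.** Maximum = 8 × 3 = 24. This matches the article.

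**Step 2. Turn the percentage into a raw score.** 0.80 × 24 = 19.2. The smallest whole total that is at least 19.2 is 20. The article's 19 is not reproduced.

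**Step 3. Turn raw scores into percentages.**

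| Total | Share of 24 | At least 80%? | At least 19? |
|---|---|---|---|
| 18 | 75.00% | no | no |
| 19 | 79.17% | no | yes |
| 20 | 83.33% | yes | yes |

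The forms disagree only at 19, which is one of the 25 possible whole totals (0 to 24).

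**Step 4. Can rounding reconcile them?** Rounding 19.2 to the nearest whole number, or truncating it, gives 19, which is the likely origin of the stated figure. But a minimum cannot be rounded down without admitting a score below it. In the other direction, 79.17% rounds to 79% at whole-percent precision, not 80%. Rounding to the nearest 10% does give 80%, but it would also lift 18/24 (75%) to 80%, and the article's raw form does not call 18 high.

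**Step 5. Fractional or averaged scores.** If totals can be fractional, or call scores are averaged, ≥80% means ≥19.2 and the forms disagree from 19.0 to below 19.2. For illustration, take the mean of six monthly totals: 6 × 19 = 114 and 6 × 19.2 = 115.2, so sums of 114 or 115 (means 19.00 and 19.17) fall in the gap.

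**Step 6. How many scores are exposed?** Nine prisons with monthly calls over 24 months give about 9 × 24 = 216 call-level scores. The article gives no distribution of scores, so the number equal to 19 is unknown and could be zero.

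**Step 7. Check the two possible repairs.** Keeping 80% with whole totals gives ≥20/24. Keeping 19 requires a percentage that 19/24 meets: 0.79 × 24 = 18.96, and the smallest whole total at or above that is 19, so ≥79% works. Writing ≥79.2% would not, because 0.792 × 24 = 19.008, which 19 misses.

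**The case against.** The strongest reply is that nothing turns on this. The article ties no decision to the label: no progression rule, retraining, site exclusion, analysis population or hypothesis test. This is a type 1 hybrid trial in which implementation factors are explored secondarily (Section 2.3). The only analysis of fidelity that the article describes, in Section 2.8.4, is exploratory and does not mention the cut-off. If the score enters as it stands, the discrepancy changes no estimate. All of that stands, and it keeps the point small.

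A second reply is that ≥19/24 may be the intended rule. It is as explicit as the percentage, it is the form a scorer would apply to a raw total, and 80% could be a loose label for it. This also stands. A reader might infer that calls scoring 19 would be wrongly classed as high, or that the raw form inflates the share of high-fidelity calls. Both readings assume that the percentage governs, and the article does not say so. It supports only that the two forms disagree at 19, and that the raw form can never label fewer calls high than the percentage form.

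A third reply is that Appendix C may allow fractional scoring. That affects which raw figure matches 80% (19.2 instead of 20), but a score of 19.0 still falls short of 80%, so the mismatch remains.

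**Conclusion.** The inconsistency is real and follows from figures within one paragraph of Section 2.7.2. 19/24 is 79.17% and 80% of 24 is 19.2, so the two forms of the cut-off classify a score of exactly 19 differently, as they do an averaged score from 19.0 to below 19.2. Nothing else in the article reconciles them.

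Its reach is narrow. It affects the descriptive high-fidelity label, and the exploratory analysis in Section 2.8.4 only if fidelity is dichotomised there. How many calls it would touch cannot be derived from the article. The primary outcome, its model and the power calculation do not depend on it. The statement that disagreement is confined to a single total rests on whole-number scoring; the existence of the disagreement does not.

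**What to change.** Make the two forms agree in Section 2.7.2 before fidelity data are summarised. Either of these does it:

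- Keep ≥80% and state ≥20/24. This assumes whole-number totals; if fractional or averaged totals are possible, state ≥19.2/24.
- Keep ≥19/24 and state the percentage as about ≥79%, with the raw score named as the governing form.

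The cost is one number in one sentence. Under the first option slightly fewer calls may be labelled high fidelity than under the raw form now printed. Under the second, the label for whole-number totals stays as the raw form already has it, and the round 80% figure is given up.
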